#### Trial 2 (community group only)

This trial includes four intervention arms, across the same four COVID-19 health messaging context areas as Trial 1.

The study arms include:

General practitioner talking head visual stimulus delivered health message (same materials as Trial 1).Animated general practitioner visual stimulus delivered health message (same materials as Trial 1).Politician visual stimulus delivered health messageWritten delivery of health message (control)

Each participant will be exposed to each of the four intervention arms (control written provision of health message, general practitioner talking head, general practitioner ’animation’, politician delivered message). The content of the messaging included in each of these four intervention arms will be held as constant as possible.

We did not use the same factorial design as we used in Trial 1 for the Trial 2 general community sample as we considered that there was no truly representative person we could use for the ‘community representative’ intervention level. We pivoted in our planning to consider the impact of general practitioners (high levels of trust) [49] to politicians (lower levels of trust) [19, 22] under the reasoning that politicians became the ‘face’ of public health messaging during the COVID-19 pandemic in Australia when others (such as general practitioners) could have been, and we desired to understand the potential consequences of this. The politician videos will be constructed from specific edits of existing publicly available footage from politicians at both state and federal levels and on different sides of the ‘political divide’ in Australia to try to limit the impact that political party preferences might have on the comparison between politicians and general practitioners for message delivery.

Like Trial 1, Trial 2 will enable comparison of animated versus talking head visual representations by contrasting Trial 2 intervention arms 1 and 2 as these will be the same videos as used in Trial 1. It will also allow examination of the moderating effect that population subgrouping (general community versus vulnerable groups) might have on the relationship between the visual representation factor and study outcomes.

The written materials will be based as closely as possible to the scripts of the videos used so as to hold content as being consistent in these contrasts. This arm (Arm 4) was selected to serve as a generic control that allows for comparison of the different video-based presentation approaches to a written information approach, that might resemble written information available on a government website.

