The project team contains a general practitioner who will perform this role for materials production. Scripting of the intervention messaging will be consistent with publicly available messages that have been forwarded by government and will be held as constant as feasible between the intervention levels. Community representatives will be specifically selected for each subgroup population based on their established leadership. They will also be invited to co-design messaging to ensure it is appropriate for the specific vulnerable population. Two of the vulnerable subgroup populations will require translation (of the written survey material) and interpreting (of the video content). This will be English to Dari and Sinhalese translation and interpretation for refugee and asylum seeker subgroup who have limited English proficiency and English to Auslan interpreting for the deaf and hard of hearing subgroup. During the video production phase, we will aim to ensure the consistency of ‘who’ across the general practitioner and community representative videos by purposely using a community representative who is recognisable and familiar to the participants. For these groups, interpretation of the general practitioner videos will be completed by a different person (who will not be as recognisable or familiar to the participants). For the refugee and asylum seeker subgroup, the general practitioner interpreter will not be visible on screen and provide spoken interpretation only, into either Dari or Sinhalese (English subtitles will remain on screen for both community representative and general practitioner videos). For the deaf and hard of hearing subgroup, the interpreter will remain on screen providing Auslan interpretation, with English subtitles also available for all videos except the community representative videos.

These contexts across which the intervention levels will be provided will be:

Having a booster vaccineWearing a mask outdoors when you can’t physically distanceStaying at home when you have a new cough symptomUsing QR check in codes when required

Video-based public health messages will be constructed to be up to 2 minutes in duration which we considered to be the upper limit of time used for public health messaging.

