### Analysis

The comparisons we will undertake across the three trials will be:

#### Trial 1

Main effect of who is providing the message (General Practitioner versus community representative).Main effect of visual stimulus (talking head versus animation).Interaction effect between these two main effects.Simple effects if interaction effect is significant.

#### Trial 2

General practitioner talking head visual stimulus delivered health message versus animated general practitioner visual stimulus delivered health message.Politician visual stimulus delivered health message versus general practitioner talking head visual stimulus delivered health message.Written delivery of health message (control) versus all other intervention types (general practitioner talking head, general practitioner animation and politician delivered health message).

#### Trial 3

The effectiveness of health information provision delivered through a conversational training approach by a general practitioner versus through a direct information provision approach by a general practitioner.

Comparisons will not be made between context areas as part of the primary analysis. However, we will investigate interaction effects of the different intervention comparisons across the different context areas and population subgroups so that we can understand whether certain interventions work better in certain contexts and populations.

Linear mixed model analyses will be used treating the intervention levels as fixed factors and participants as random factors. Context will be ignored when investigating intervention main effects as it will be balanced across the different intervention levels.

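### The cross-trial test of whether population moderates the animation versus talking-head effect presumes identical GP videos, but two of the six vulnerable subgroups are shown interpreted versions, so a pooled difference cannot be put down to population alone

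*Protocol article*

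**What the plan says.** Protocol article, Trial 2 (community group only): the talking-head and animated GP arms are each listed as using the Trial 1 materials. The text adds that the animation versus talking-head comparison parallels Trial 1, "as these will be the same videos as used in Trial 1". The next sentence names a second question that the design can address: "moderating effect that population subgrouping (general community versus vulnerable groups) might have on the relationship between the visual representation factor and study outcomes".

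Protocol article, Trial 1 (vulnerable groups only): two of the six vulnerable subgroups need the video content interpreted.

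- For participants who are refugees or people seeking asylum: "the general practitioner interpreter will not be visible on screen and provide spoken interpretation only, into either Dari or Sinhalese". Subtitles in English are kept.
- For Auslan users: "the interpreter will remain on screen providing Auslan interpretation, with English subtitles also available for all videos except the community representative videos".

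The Procedure section repeats that video information is adapted to the communication needs of the subgroups. The Analysis section lists, for Trial 1, the two main effects, their interaction, and simple effects if that interaction is significant. It then says in general terms that intervention effects will be examined for interaction with context and population subgroup. Neither the Analysis section nor the Limitations mentions that the stimulus differs between populations.

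**The concern.** Comparing the format effect across populations is informative about population only if both populations see the same two formats. Here the difference touches the factor under study. An on-screen interpreter adds a human figure to whichever video is shown, including, as far as the text says, the animation. An unseen interpreter replaces the voice of a presenter whose face is visible, while an animation with voice-over has no such mismatch. So it is plausible, though not shown, that interpreting acts differently on the two formats.

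At stake is the conclusion that may be drawn. The Discussion raises the prospect of one animation reused across all groups if effects are similar. A moderation result produced by interpreting, or a true one masked by it, would mislead that decision. Within the two interpreted subgroups every GP video is interpreted, so no model fitted to these data can separate population from adaptation there.

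**Working it through.** **Inputs from the plan.** Six vulnerable subgroups, two of them interpreted (Participants and setting; Trial 1). Sample size section: 36 per subgroup, 40 recruited, about 10% partial completion, proportions 0.2 and 0.4, correlation 0.61, two-sided alpha 0.05, 80% power. No maximum is set for the community sample.

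**The plan's own figure.** It matters here only because it fixes the subgroup sizes.

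- Both-positive cell: 0.2 × 0.4 + 0.61 × √(0.2 × 0.8 × 0.4 × 0.6) = 0.1995.
- Discordance: (0.2 − 0.1995) + (0.4 − 0.1995) = 0.2009 before rounding of the cells.
- McNemar normal approximation: n = (1.96√0.2009 + 0.842√(0.2009 − 0.04))² / 0.04 = 36.98, against 36 stated. Power at 36 by the same formula is 78.9%.
- Recruitment: 36 / 0.90 = 40, as stated.

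The figure is reproduced to within one participant and is not in question.

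**Share affected.** 2 × 40 = 80 of 6 × 40 = 240, or 33%.

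**Effect on the pooled moderation estimate.** Let d be the animation minus talking-head effect in the GP cells, equal in the community and in every vulnerable subgroup (no true moderation). If interpreting adds a₁ to the response to animation and a₂ to the response to the talking head, the contrast in an interpreted subgroup becomes d + h, with h = a₁ − a₂. If a₁ = a₂, then h = 0 and nothing is distorted, because each participant sees both formats.

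Pooled over the vulnerable groups: (160 × d + 80 × (d + h)) / 240 = d + h/3. The community estimate is d, so the apparent moderation is h/3. If the two subgroups have different shifts, h is their average, and opposite signs partly cancel.

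| Assumed h (difference in proportions) | Shift h/3 |
|---|---|
| 0.05 | 0.017 |
| 0.10 | 0.033 |
| 0.20 | 0.067 |
| 0.30 | 0.10 |

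Every value of h is an assumption; the documents give none.

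**Without the interpreted subgroups.** The shift is zero, with 4 × 40 = 160 recruited (4 × 36 = 144 completing).

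**Precision given up.** Take 0.2009 as the variance of a within-person difference (the planning discordance) and an assumed community sample of 216 or 1,000. The difference in format effect detectable with 80% power is 2.80 × √(0.2009/n_v + 0.2009/n_c):

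| Community (assumed) | All six subgroups, n_v = 216 | Four subgroups, n_v = 144 |
|---|---|---|
| 216 | 0.121 | 0.135 |
| 1,000 | 0.094 | 0.112 |

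**The case against.** The case on the other side has real strength. The interpreting is disclosed in detail in the Trial 1 section, and the statement about identical videos can be read as the same GP footage with access features added. That statement is also attached to the format comparison, with moderation following in the next sentence. Moderation is not among the listed comparisons; the Analysis section covers population only through general interaction tests. Those tests are by subgroup and the sample size is set for single subgroups, so results for the two interpreted groups need not be buried in a pooled estimate. Interpreting is how these groups would receive such messages, and dropping them changes the question from vulnerable groups to four selected ones. Nor would the remaining comparison be perfectly clean: the Procedure section's wording on adaptation is broad, and population is not randomised.

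Most of this limits the point without removing it. Disclosure in one section does not make the premise in the next one true, and subgroup interactions still cannot tell population from adaptation in the two interpreted groups. The objection to making four subgroups the main analysis does stand, so both versions should be reported.

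A reader might go further and infer that the Trial 1 format effect, averaged over GP and community-representative videos, will be set against a GP-only effect in Trial 2. The documents do not say this. The Trial 2 section points to the shared GP arms, and the Analysis section lists the interaction and conditional simple effects, which include the GP-only effect. What remains is that this effect is listed only if the interaction is significant, so stating GP cells outright is worthwhile.

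**Conclusion.** The concern holds as a false stated premise under a named, non-primary analysis. For about a third of the target vulnerable sample the GP videos are not those shown to the community, and a difference in those subgroups is population plus adaptation. The resulting shift in the pooled GP-only estimate is about h/3, or 0.017 to 0.10 over the assumed range. This rests on equal subgroup sizes and on interpreting acting differently on the two formats, which is plausible but undocumented.

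Three stronger readings are not supported. Population is not wholly confounded with stimulus, since no interpreting is described for the other four subgroups. The animation versus talking-head contrast within Trial 1 and within Trial 2 is not affected by this point. And the shift should not be scaled against the 0.2 to 0.4 planning difference, which refers to a paired contrast inside one subgroup, not to moderation across trials.

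**What to change.** 1. In the Trial 2 section, correct the statement about shared videos so that it agrees with the Trial 1 section: the GP footage is shared, with interpretation added for the refugee and asylum-seeker subgroup and for the Deaf and hard of hearing subgroup.
2. State that the cross-trial moderation analysis uses only the GP talking-head and GP animation cells of Trial 1, whether or not the Trial 1 interaction is significant.
3. Report it with all six vulnerable subgroups and again with the two interpreted subgroups excluded.
4. Report those two subgroups separately, labelled as population plus adaptation, and attribute a difference to population only if it persists without them.

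The interpreting itself should stay, as it is needed for access. The cost is a few sentences and one additional analysis on data already being collected. The restricted version is less precise (about 160 instead of 240 vulnerable participants) and speaks to four subgroups only, so failure to persist there may reflect lower precision and should be read with its confidence interval.

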#### Trial 3 (all participants)

Trial 3 will include two intervention arms across two different context areas related to COVID-19 health. The two arms of the study will be:

Conversational training approach provided by a general practitioner (talking head).Direct information provision provided by a general practitioner (talking head).

The arms of study differ by the language, content and tone. The conversational training approach provides a health message in a peer-to-peer fashion that is expressed in a relaxed conversational tone. The direct information provision arm, provides a health message that is direct and didactic in style, and does not provide suggested statements that people could say in a discussion with another person on this topic.

The two context areas will be:

Encouraging people who have workers coming to visit them at home to ask them if they are vaccinated or not.Encouraging people to avoid sharing food, utensils and other items at gatherings.

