## Materials & methods

### Design

The Standard Protocol Items: Recommendations for Interventional Trials (SPIRIT) flow diagram schedule of enrolment, interventions and assessment procedures is provided in Fig 1 [38]. We will conduct three concurrent ‘helix’ randomised controlled trials (Figs 2–4), as approved by Monash University Human Research Ethics Committee on the 8^th^ April 2022 (HREC 30698). The Helix design is a counterbalanced, randomised controlled trial that involves allocating participants to each level of an intervention, but spread across different context areas. The outcome measure is repeated for each intervention level / context area exposure, allowing for a pooled analysis with repeated measures within participants. This enhances statistical power of an investigation while minimising the risk of intervention-level contamination by separating them across the different context areas.

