**Fig 4 pone.0280865.g004:**
[figure not shown]
Visual representation of the helix randomised control trial design for Trial 3. C1 denotes combination 1, C2 denotes combination 2, Individual participants are exposed to the combinations of intervention level / context areas within a vertical combination column.

In trial 1, we will combine the ‘helix’ approach with factorial allocation of intervention levels. In all trials we will be using Latin-square sequencing of the intervention levels to minimise the risk of order effects from potentially biasing the contrasts between intervention levels. Participants will be exposed to context areas in a set order (meaning that order effects could impact contrasts between them) as comparisons between contexts are not of primary interest in these investigations.

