#### Primary outcome 2: Stated intention to encourage family or friends to undertake a context specific behaviour

Participants will be asked their intention to encourage family or friends to undertake a context specific behaviour after viewing the intervention. Responses will be scaled using a 5-point Likert Scale (‘much less inclined’, ‘less inclined’, ‘about the same’, ‘more inclined’ and ‘much more inclined’). Levels of trust in family or friends has been shown to be similar to other sources regarding COVID-19 information.(23) This level of trust, combined with the high levels of opportunity for conversations to take place between family and friends regarding public health measures makes this arguably an important outcome to influence.

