### Study timeline

Participants will be able to access the relevant survey (to their subgroup) leading to either Trial 1 then Trial 3 (combined) or Trial 2 then Trial 3 (combined) independently or with assistance from the corresponding Partner Organisation. By following the link to the corresponding survey for each subgroup population, participants will have access to the explanatory statement including inclusion and exclusion criteria. From there, participants can choose to participate and confirm they adhere to the inclusion criteria. The data collection and survey builder software Qualtrics (Qualtrics, Provo, UT, USA) will automatically, randomly allocate participants into one of four potential combinations of allocation using a Latin Square approach for both Trial 1 and Trial 2, (minimising study level order effects), and will again randomly assign to one of two possible combinations for Trial 3. Data will be extracted for analysis purposes with no follow-up period required. Refer to Fig 1 for an overview of the study timeline.

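### Trial 3's pooled contrast absorbs half of any carry-over between its two messages, and the planned intervention-by-context interaction cannot separate carry-over from context

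*Protocol article*

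**What the plan says.** Layout. The Trial 3 section under Interventions states: "Trial 3 will include two intervention arms across two different context areas related to COVID-19 health". Both arms are general practitioner talking heads. The direct arm "does not provide suggested statements that people could say in a discussion with another person on this topic". Under Study timeline, the survey software "will again randomly assign to one of two possible combinations for Trial 3". The Sample size section says that the study takes place in a single session.

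Safeguards. The Design section claims that the helix layout works by "minimising the risk of intervention-level contamination by separating them across the different context areas". The Design text after the figure legends adds: "In all trials we will be using Latin-square sequencing of the intervention levels to minimise the risk of order effects". It then says: "Participants will be exposed to context areas in a set order (meaning that order effects could impact contrasts between them"; this is accepted because contexts are not the comparison of primary interest.

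Analysis. One Trial 3 comparison is listed, beginning "The effectiveness of health information provision delivered through a conversational training approach by a general practitioner" and set against the direct approach. The model is a linear mixed model with participants as random factors. Context is left out of the main-effect analysis on the ground that it is balanced across intervention levels. Intervention-by-context and intervention-by-population interactions are also planned, to learn whether some interventions work better in some contexts or populations.

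Outcome most exposed. For primary outcome 2: "Participants will be asked their intention to encourage family or friends to undertake a context specific behaviour after viewing the intervention".

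**The concern.** With two arms, two contexts in a fixed order and two combinations, every participant follows either conversational-then-direct or direct-then-conversational. Whenever the direct message comes second, it follows the conversational one. A two-sequence Latin square balances position. It does not balance what came before.

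Separating contexts protects best when the content of a message is useful only in its own context. One Trial 3 arm is described as training in conversation and appears to supply things to say to other people. If any of that transfers, it would most plausibly touch primary outcome 2, which concerns encouraging others.

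Two things are at stake: the size of Trial 3's single comparison, and the meaning of a Trial 3 intervention-by-context interaction. On the plan's stated purpose, such an interaction would be reported as the approach working better in one context, when it could equally be carry-over from the first message.

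**Working it through.** **Inputs from the protocol.** Two arms, two contexts and two combinations; set context order; single session; 36 participants per subgroup (40 recruited); six vulnerable subgroups; proportions 0.2 versus 0.4; correlation 0.61; two-sided alpha 0.05.

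**Assumptions.** Allocation to the two combinations is 1:1 (no ratio is stated). Carry-over is expressed as a fraction c of the effect; the protocol gives no value, so a range is shown. Effects are on the proportion scale of the Sample size section, although the analysis will be a linear mixed model.

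**1. The plan's own figure.** With correlation 0.61, the probability of a positive response on both is 0.2 × 0.4 + 0.61 × √(0.2 × 0.8 × 0.4 × 0.6) = 0.1995. The discordant cells are 0.0005 and 0.2005, total s = 0.2009. The McNemar sample size is n = [1.96√s + 0.842√(s − 0.2²)]² / 0.2² = 36.98. The stated 36 is reproduced to within one participant (power at 36 is 78.9%). The sample-size figure is not at fault.

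**2. What the pooled contrast estimates.** Let d be the true effect, p the difference between second and first position (which is also the difference between contexts), and λ the carry-over from a first conversational message minus that from a first direct message.
- Conversational first: conversational minus direct = d − p − λ.
- Direct first: conversational minus direct = d + p.
- Average: d − λ/2.

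Balance cancels p but leaves λ/2. With λ = cd the estimate is d(1 − c/2).

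| c | pooled estimate, d = 0.20 | first-message effect | second-message effect | apparent interaction | paired power, n = 36 |
|---|---|---|---|---|---|
| −0.25 | 0.225 | 0.20 | 0.25 | −0.05 | 84% |
| 0 | 0.20 | 0.20 | 0.20 | 0 | 79% |
| 0.25 | 0.175 | 0.20 | 0.15 | 0.05 | 67% |
| 0.5 | 0.15 | 0.20 | 0.10 | 0.10 | 54% |
| 1 | 0.10 | 0.20 | 0 | 0.20 | 28% |

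(Power holds the correlation at 0.61 where feasible.)

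**3. Aliasing.** The context-1 effect is d and the context-2 effect is d − λ, so the intervention-by-context interaction equals λ. A genuine interaction of the same size gives the same means. In a large simulation with d = 0.5, carry-over of 0.25 and no interaction gave pooled/first/second effects of 0.37/0.50/0.24. A genuine context interaction of −0.25 and no carry-over gave 0.38/0.51/0.25. The data cannot tell them apart.

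**4. Chance of seeing the interaction at all.** This is a between-sequence test on the sum of the two responses. The variance of the sum is 0.16 + 0.24 + 2 × 0.61 × √(0.16 × 0.24) = 0.639, and with N participants the standard error is √(0.639 × 4/N). For c from 0.25 to 1, power is 5-12% at 36 to 40 participants and 8-49% at 216 to 240.

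**5. First-message comparison.** Between participants, with m per sequence, power = Φ([0.2√m − 1.96√(2 × 0.3 × 0.7)] / √(0.16 + 0.24)).
- One subgroup: 25% (m = 18), 28% (m = 20).
- Six vulnerable subgroups pooled: 6 × 36 = 216, m = 108, 90%; 6 × 40 = 240, m = 120, 93%. The community sample would add to this.
- 80% power needs m = 82 (91 with continuity correction).

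**The case against.** The strongest case against has four parts.

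**The authors saw contamination coming and designed against it.** They put each level in a different context, the suggested statements are tied to the topic at hand, the two topics differ (vaccination of visiting workers; sharing items at gatherings), and both primary outcomes are context specific. Outcome questions also follow each message, so the two videos are not back to back. This stands as a reason to think carry-over may be small. It does not make the contrast free of it, because balance and a two-sequence square leave λ/2 whatever its size.

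**A reader might infer that the effect will be shrunk, and undetectably.** The documents do not support that. They give no sign: a didactic message may look worse after a conversational one, which would enlarge the contrast. Nor would carry-over be invisible. It would appear in the planned interaction, though with low power and under the label of a context effect.

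**A reader might also infer that the plan offers no unaffected comparison.** Because context order is fixed, the context-1 effect from the planned interaction analysis is the first-message contrast. What the protocol does not do is identify it as such. A sensitivity analysis may sit in an analysis plan that is not shown, so its absence from the article is not the point. The point is the stated reasoning that separation and balance suffice, and the stated reading of the interaction.

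**A tempting remedy does harm.** Basing the conclusion on the first message whenever the within-person estimate looks smaller is data-driven. In simulation with no effect and no carry-over (216 participants, correlation 0.61), type I error rose from 5.0% to between 7.6% and 9.3%, depending on the threshold. This objection stands in full.

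**Conclusion.** The point holds in a limited form. Trial 3 is an AB/BA crossover with position and context confounded, and its pooled contrast carries a bias of half the differential carry-over. On the plan's own 0.20 difference, assumed carry-over of 25% to 100% gives 0.175 to 0.10, and carry-over of −25% gives 0.225. These sizes rest on assumed values of c, 1:1 allocation and additive effects; the protocol does not say that carry-over exists, how large it is or which way it runs. Primary outcome 2 is the more exposed, by inference from the description of the arms.

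What follows without any assumption about c is the aliasing: a Trial 3 intervention-by-context interaction cannot be attributed to context rather than carry-over.

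The first Trial 3 message is free of carry-over within Trial 3 only. It always follows Trial 1 or Trial 2, but that earlier exposure is balanced by the separate Trial 3 randomisation.

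**What to change.** In the Trial 3 part of the Analysis section:

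1. Name the comparison of conversational versus direct on the first Trial 3 message (context 1) as a sensitivity analysis for both primary outcomes. It is between participants, pooled over populations and stratified by population, and is reported beside the within-person estimate.
2. State that a Trial 3 intervention-by-context interaction may reflect carry-over and will not be interpreted as a context effect alone.
3. Keep the within-person contrast as the main analysis, with no rule that moves the conclusion from one estimate to the other on the observed results.

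The cost is one extra analysis of data already collected. Its limits should be stated: it covers one context, its interval is wider than that of the within-person estimate, and it is informative only when pooled, not in the single subgroups for which the sample was sized.
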